## Abstract

**Clinical Trial Registration:**

clinicaltrials.gov, identifier NCT06765200.

## Introduction

1

Chronic pain in adolescents is a significant and growing concern. Research has shown that the prevalence of chronic pain in adolescents is high and increasing (1, 2), including the most severe cases, that is, those with the highest levels of pain intensity and interference (3). A recent review reported that prevalence rates vary depending the study, however, it is estimated that about 25% of adolescents report chronic pain (4). This condition leads to substantial impairments in physical (e.g., sleep) and psychological (e.g., depression) well-being (5, 6), affecting their cognitive function (7) as well as school performance (8). Moreover, it also interferes with their social function (9, 10).

There is widespread consensus that a psychosocial approach is essential for maintaining or improving the functioning and well-being of adolescents with chronic pain (11, 12). However, the availability of evidence-based psychosocial treatments for adolescents with chronic pain is insufficient to meet the high demand, particularly in areas outside large cities. The reasons vary, but one of the main barriers is the shortage of professionals trained to attend the demands (13). As a result, many adolescents endure chronic pain without the necessary support for satisfactory daily functioning and quality of life, highlighting a severe inequality in access to adequate care (14). Due to this shortage of treatment programs, many adolescents with chronic pain are attended first by primary care physicians (15). These physicians, however, typically refer patients to specialized programs, leading to unnecessary delays as patients face long waitlists to receive proper specialized care (16, 17).

Digital health, defined as “the field of knowledge and practice associated with the development and use of digital technologies to improve health” (18), provides new opportunities to increase the reach of evidence-based psychosocial interventions for chronic conditions, including chronic pain. Digitally delivered psychosocial interventions have shown similar effects to standard (face-to-face) treatment for conditions such as anxiety and depression (19), and the empirical support for digital health in the field of chronic pain is rapidly increasing (20, 21). Digitalization represents a paradigm shift in healthcare with dramatically improved opportunities to increase patient access, equality, and equity (22). However, evidence-based digital health treatments are not available for chronic pain patients in regular care, including adolescents, outside clinical trials (23, 24).

### Objectives

1.1

The overarching objective of this project is to help reduce the pain impact in adolescents with chronic pain and improve their functioning. We aim to achieve this by developing and implementing DigiDOL-Ad, a novel and reliable digital treatment (i.e., mobile application). With DigiDOL-Ad we aim to empower patients to better manage and cope with their chronic pain. In addition, this new app will be complemented by websites with resources and information, one specifically developed for parents or main caregivers and another for teachers. This article describes the protocol created for this project and follows the Standard Protocol Items: Recommendations For Interventional Trials (SPIRIT) guidelines (25) (see Supplementary Appendix 1 for the WHO Trial Registration Data Set information).

In pursuit of this goal, the project will evolve with specific objectives:
1.Improve the understanding of the needs of all stakeholders—adolescents with chronic pain, their parents/tutors, attending physicians, teachers, and health authorities—regarding the management of chronic pain and the features of DigiDOL-Ad. We expect to find many important, specific to each group, and shared, unmet needs (Hypothesis 1).2.Co-create a scientifically validated and evidence-based, patient-centered digital treatment for adolescents with chronic pain, involving all stakeholders: adolescents with chronic pain, parents, attending physicians, teachers, and health authorities. We expect that the digital treatment will be found user-friendly, and liked by all participants (Hypothesis 2).3.Evaluate DigiDOL-Ad in helping adolescents adjust to and manage chronic pain. We anticipate that adolescents with chronic pain using DigiDol-Ad will report statistically significant improvements in chronic pain and physical and psychosocial functioning after treatment, maintained at follow-up (Hypothesis 3).4.Assess whether the active involvement of parents and teachers, facilitated through dedicated companion websites, as change agents, that contribute to improved outcomes in adolescents with chronic pain. We hypothesize that adolescents whose parents and teachers actively engage with the digital treatment will experience greater improvements in pain management and quality of life compared to those with less engaged support (Hypothesis 4).

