#### Phase 4. Evaluation study of DigiDOL-Ad

2.2.4

In this last phase, we will evaluate DigiDOL-Ad. This will be a multi-site study with 8 hospitals referring potential participants. The procedure will begin with adolescents and their parents responding to a battery of questionnaires. This assessment will be conducted online, to decrease biases due to social desirability effects. We will use the *REDCap System* (34) to implement the online assessment, which allows for programing follow-ups at the different data collection points. Participants will be assessed three times: Pre- and Post-treatment (T1, T2) and 3-months follow-up (T3, adolescents only). After completing T1 assessment, participants will receive access to DigiDOL-Ad (adolescents) and to the webs (parents and teachers).

Participants will receive written instructions detailing how to access the treatment. Each participant will be assigned a unique username and password, which will be linked to their participant ID. This linkage will facilitate the monitoring of participants' adherence.

To maximize retention of participants the project will simplify accessibility and provide easy-to-understand instructions for downloading, accessing, and using the app. In addition, reminder emails with personalized and motivational messages will be sent at each assessment point. Moreover, we will conduct periodic surveys or check-ins every week to identify barriers to participation, such as time constraints or usability issues, and participants will receive compensation for completing the surveys. In addition, to maximize engagement from the healthcare professionals, they will receive information on the study progress and preliminary findings -when possible- using periodic newsletters to sustain interest. Moreover, they will be informed about the referral and enrolment volumes per hospital, emphasizing the value of their contribution to the study and its potential impact on improving chronic pain management in adolescents. Importantly, the project will acknowledge participants' efforts through individual thank-you notes and public acknowledgment in study updates. Finally, the project will build trust and rapport by facilitating transparent communication with a study coordinator to build a personal connection with participants.

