In this study, the sample will include adolescents with chronic pain and one of their parents. Based on a within-subjects repeated measures ANOVA with three time points (baseline, post-treatment, and 3-month follow-up), we will use GPower (version 3.1.9.7) to calculate the required sample size. We set a small effect size (f = 0.10), with a two-tailed alpha of 0.05 and power of 0.80. For the calculation, the following parameters were assumed: number of measurements = 3 (baseline, post-treatment, and 3-month follow-up), correlation among repeated measures = 0.5, and nonsphericity correction epsilon = 1. This calculation indicated that a sample of *N* = 163 dyads would be sufficient. However, in order to prevent attrition issues, we will be recruiting a minimum of 195 dyads -minimal attrition is expected based on prior studies on digital treatments with similar populations (37). Recruitment is expected to proceed at a rate of approximately 5 participants per month, based on projections from similar previous studies [e.g., (30)]. To account for potential variability, we conservatively estimate a recruitment rate of 2 adolescents per month per hospital. With 8 hospitals participating, this would result in enrolling the required sample of 352 participants within 22 months. An additional 5 months will be allocated for participants to complete the treatment (approximately 8 weeks, as previously described) and the 3-month follow-up, bringing the total duration for recruitment, enrollment, and follow-up to 27 months.

In order to ensure that the target sample size is reached in the evaluation study, the following strategies will be implemented: (a) using clear and engaging messages (i.e., developing age-appropriate, visually appealing recruitment materials, like posters, flyers, or videos to be shared by hospitals and healthcare professionals); and (b) highlighting the benefits of participation, such as improving their own pain management and contributing to advancements in adolescent healthcare. Moreover, we will offer both monetary and non-monetary incentives (i.e., certificates of participation and feedback on their progress). To enhance participant retention and ensure completion of follow-ups, we plan to implement personalized reminders. These reminders will be delivered via app notifications, SMS, or email, and will serve to notify participants of upcoming tasks or scheduled follow-up activities.

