### Outcomes and measures

2.4

The outcomes used are based on the recommendations of a recent consensus study involving several stakeholders [children with chronic pain, parents, healthcare experts and researchers; (38)]. The main outcomes of the evaluation study are pain intensity, pain interference and the global impression of change after treatment. In addition, we will collect information from a group of secondary outcomes. To capture the overall impact of the intervention, we will assess global impression of change using a standardized measure as suggested in the Core Outcomes in Pediatric Persistent Pain Workgroup (39).

Both adolescents and their parents will respond to an online survey including questions about sociodemographic characteristics, concomitant treatments and pain medication (type and doses). In addition, adolescents will complete the following outcome measures: pain intensity [NRS-11; (40)], pain interference [PROMIS Pediatric Pain Interference; (41)], pain-related self-efficacy [PSEQ; (42)], concerns about pain [UW-CAP; (43)], pain attitudes [Peds-SOPA; (44)], functional disability [FDI; (45)], anxiety [PROMIS Pediatric Anxiety; (46)], depressive symptoms [PROMIS Pediatric Depression; (46)], sleep disturbance [PROMIS Pediatric Sleep disturbance; (47)], fatigue [SFS; (48)], treatment expectancies (49), treatment perceptions [perception of how easy to use and how helpful the skills taught are; (50)], adherence (i.e., use of DigiDOL-Ad and of the skills learned with treatment), global impression of change after treatment (38), satisfaction with treatment (51) and adverse effects (52).

In addition, the parents' online survey will include the following outcome measures: functional disability [FDI; (45)], treatment expectancies (49), satisfaction with treatment (51), and global perception of change after treatment (38). Figure 2 provides details of the SPIRIT schedule of enrolment, intervention and assessments.

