### Data analysis

2.5

We will use descriptive statistics to describe the sample (i.e., means, standard deviations, and percentages). To study the outcomes of the FGs, we will use a deductive content approach to synthetize the information. After transcribing the sessions, they will be coded, and results extracted and summarized. To study intervention effects, we will perform repeated measures ANOVAs, as described in section 2.3. Effect sizes will be estimated using partial eta squared (*η*ₚ²) for the repeated measures ANOVA, which is recommended for within-subjects designs. In cases where pairwise comparisons are conducted, Cohen's d will be reported to facilitate interpretation of the magnitude of differences. The analysis will follow and intent-to-treat approach, including all participants who initiated the digital treatment, regardless of their level of adherence to the protocol. For handling missing data, multiple imputation methods will be employed to account for potential biases and ensure the robustness of the results. The software IBM SPSS Statistics for Windows will be used.

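### Hypothesis 4 cannot be tested as worded: no quality-of-life instrument, no parent or teacher engagement variable, and no teachers in the stated sample

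*Protocol article*

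**What the plan says.** Section 1.1 makes this one of four specific objectives. Hypothesis 4 states that "adolescents whose parents and teachers actively engage with the digital treatment will experience greater improvements in pain management and quality of life". The reference group is adolescents whose support is less engaged. It is a comparison between adolescents, with engagement of both parents and teachers as the exposure.

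The sections that describe the evaluation study provide the following:

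- **Sample (2.3):** "the sample will include adolescents with chronic pain and one of their parents".
- **Who is assessed (2.2.4):** the procedure starts with "adolescents and their parents responding to a battery of questionnaires". After the first assessment, "participants will receive access to DigiDOL-Ad (adolescents) and to the webs (parents and teachers"). The same section gives each participant a log-in tied to the participant ID, to help monitor adherence.
- **Usage measure (2.4):** the list of adolescent measures includes "adherence (i.e., use of DigiDOL-Ad and of the skills learned with treatment").
- **Parent measures (2.4):** the parents' "online survey will include the following outcome measures: functional disability [FDI; (45)], treatment expectancies (49), satisfaction with treatment (51"), plus a global perception of change.
- **Analysis (2.5):** for intervention effects, "we will perform repeated measures ANOVAs, as described in section 2.3". Section 2.3 describes a within-subjects design with three time points.

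**The concern.** A hypothesis of this kind needs an outcome that is measured, an exposure that is recorded, and people in whom both are observed. Set against the sample and the list of measures, Hypothesis 4 has gaps in each. Quality of life has no instrument. Parent and teacher engagement has no named variable. Teachers are half of the exposure but are outside the stated sample.

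These are gaps in what is collected, so an analysis plan written later could not close them by adding a model. One of the four hypotheses would have to be reinterpreted at the reporting stage, with the outcome and the meaning of actively engaged still open.

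Interpretation is a second problem. Families choose how much they engage after baseline. More engaged parents may have adolescents who differ in severity, motivation or circumstances, so a difference in improvement would not by itself show that parents or teachers acted as agents of change.

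**Working it through.** **1. Hypothesis against what is collected**

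| Element of Hypothesis 4 | What the article provides | Status |
|---|---|---|
| Quality of life | Pain intensity, pain interference, self-efficacy, concerns about pain, pain attitudes, functional disability (FDI), anxiety, depression, sleep, fatigue, expectancies, treatment perceptions, adherence, global change, satisfaction, adverse effects (2.4) | No quality-of-life instrument; related domains only |
| Parent engagement | Parent list has FDI, expectancies, satisfaction and global change (2.4); ID-linked log-ins (2.2.4) | Possibly recoverable from logs; not named as a variable |
| Teacher engagement | Website access (2.2.4); no teacher measure (2.4); sample is adolescent and one parent (2.3) | Not named; log-in status unclear |
| Engaged versus less engaged | Not defined | Open |

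**2. The plan's sample size**

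Inputs from section 2.3: f = 0.10, m = 3 measurements, ρ = 0.5, ε = 1, α = 0.05, power 0.80. For one group with a within-subjects time effect:

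- λ = f² · N · m · ε / (1 − ρ) = 0.01 × 163 × 3 / 0.5 = 9.78
- df1 = 2, df2 = (163 − 1) × 2 = 324
- power = 80.2%

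N = 163 is the smallest N that reaches 80%, so the stated figure reproduces. It is for the time effect alone and contains no engagement term.

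**3. Illustrative precision for an engagement comparison**

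The article gives no engagement split and no expected difference, so both are assumptions here.

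- SD of pre–post change = √(2(1 − ρ)) = √(2 × 0.5) = 1 outcome SD.
- With adjustment for baseline, residual SD = √(1 − ρ²) = √0.75 = 0.87 SD.
- Detectable difference at 80% power = (1.960 + 0.842) × SD × √(1/n₁ + 1/n₂), with n₁ + n₂ = 163.
- Even split: √(2/81.5) = 0.157; 2.802 × 0.157 = 0.44 SD unadjusted; 0.44 × 0.87 = 0.38 SD adjusted.

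| Split | Unadjusted change | Baseline-adjusted (× 0.866) | Power for 0.3 SD, unadjusted |
|---|---|---|---|
| 50:50 | 0.44 SD | 0.38 SD | 48% |
| 30:70 | 0.48 SD | 0.41 SD | 42% |
| 20:80 | 0.55 SD | 0.48 SD | 33% |
| 10:90 | 0.73 SD | 0.63 SD | 21% |

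**4. Cross-check with the plan's own f**

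A balanced two-group engagement-by-time interaction at f = 0.10 has df2 = (163 − 2) × 2 = 322 and power 80.2%. The stated N is therefore not wrong for every version of this comparison. The answer depends on the difference assumed and on how evenly engagement divides.

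**The case against.** The strongest reply is that this is a journal article condensing a fuller protocol, and that a statistical analysis plan may exist. Section 2.5 describes the analysis of intervention effects and does not claim to be the only analysis. An engagement term, or a definition of engaged, could properly sit in an unseen document. That stands: the missing model term, taken alone, is not an error.

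A reader might also infer that the study will hold no data at all on Hypothesis 4. The text does not support this. Parents are half of each dyad, and participants' log-ins are linked to an ID for adherence monitoring, so parent website use is plausibly recorded. Nor is it settled that teachers have no linked log-in: section 2.2.4 names them among those given access, while section 2.3 leaves them out of the sample. The schedule in Figure 2 is not shown and could not be checked.

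Two further points stand in part. Several domains close to quality of life are measured, so that gap can be closed by rewording. And section 3.2 already concedes that a single-group design limits attribution to the treatment, although it does not mention self-selected engagement.

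The reply does not reach the list of measures and the stated sample. A later analysis plan can add a model, but it cannot supply quality-of-life scores or teacher data that were not collected.

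**Conclusion.** Hypothesis 4 is not testable in its present wording. This is firm for quality of life. For teachers it rests on the stated sample and the absence of any teacher measure, with their log-in status unclear. For parents the conclusion is narrower: the exposure may exist in the logs but is not named. Hypothesis 3 and the stated N of 163 are unaffected.

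A reader might conclude that the study is underpowered for Hypothesis 4. The documents do not establish that, because they state neither a split nor a target difference. The figure of about 0.44 SD is illustrative: it assumes 163 analysed, an even split, unadjusted change and ρ = 0.5. It falls to about 0.38 SD with baseline adjustment and rises with uneven splits. Neither figure carries over directly to a continuous exposure.

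A reader might also want to treat the adolescent's app use as a confounder. Section 2.2.3 says the parents' site is meant to help adolescents move through the treatment, so app use may be a route by which parental engagement works. Adjusting for it in the main model could remove part of the effect that is hypothesised.

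**What to change.** 1. Restate Hypothesis 4 as exploratory and associational, giving self-selected engagement as the reason.
2. Replace quality of life with outcomes that are collected, for example pain interference, FDI and pain self-efficacy.
3. Name parent website use, taken from the ID-linked log-ins, as a continuous exposure.
4. Either link teacher log-ins to the adolescent's ID or drop teachers from the hypothesis.
5. Prespecify a time-by-parent-engagement model adjusted for the baseline score. Examine the adolescent's app use only in a sensitivity analysis, as a possible mediator.
6. If a precision figure is given, label it illustrative and state its split, its adjustment and the correlation assumed.

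The cost is revised objective wording, use of web logs, one extra model, and teacher log-in linkage if teachers are kept. The claim becomes weaker: an association rather than evidence that parents or teachers caused the improvement.

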## Materials and methods

2

### Study design

2.1

This is a study involving 4 phases with specific procedures (see Figure 1). The study design follows the Medical Research Council (MRC) Framework for developing and evaluating complex interventions (26).

**Figure 1 F1:**
[figure not shown]
Summary of study procedures.

### Procedure: description of the study's phases

2.2

#### Phase 1. Preparation: laying the groundwork for future studies

2.2.1

This phase is critical to establishing a solid foundation for the app's development and ensuring the quality of subsequent studies. The preparatory actions involve several key steps, focusing on collaboration, logistical planning, and resource alignment, including: (a) establishing partnerships with healthcare professionals (i.e., attending physicians) and hospitals (i.e., scheduling meetings to explain the project objectives and gather insights; partnering with hospitals to act as research sites and recruitment hubs for study participants); (b) obtaining ethical and logistical approvals to ensure that the project complies with ethical standards and is logistically viable (i.e., submitting the project proposal to institutional review boards and ethics committees for approval; developing consent and assent materials tailored to adolescents and their guardians); (c) developing study protocols to guide empirical studies and ensure consistency in data collection (i.e., defining participant inclusion and exclusion criteria; drafting standardized procedures for introducing the app to potential participants, including how instructions will be provided and how data will be collected; developing contingency plans to address potential challenges, such as dropout or technical issues); and (d) process pilot testing to refine protocols and ensure all systems are functioning optimally before full-scale implementation (i.e., testing recruitment processes, consent procedures, and data collection tools; making necessary adjustments to the protocols and app design based on feedback from pilot phase).

#### Phase 2. Co-creation of DigiDOL-Ad

2.2.2

This phase focuses on identifying the needs of all stakeholders. We will develop the DigiDOL-Ad with co-creation and user involvement at all phases to identify real user needs and design the treatment to meet these needs. The co-creation process for the mobile app will leverage insights from focus groups (FGs) to ensure the app is user-centered, inclusive, and tailored to meet the needs of adolescents with chronic pain and all stakeholders involved in managing chronic pain. The protocol for this phase will address participant diversity (i.e., FGs will be gender balanced, and include participants from different backgrounds and varying levels of digital literacy) and integration of feedback into the app development process to design an app that is practical, engaging, and effective.

Each FG will take between 60 and 90 min. In these sessions, participants will be asked to report about: (a) current challenges and unmet needs in relation to managing pain, (b) desired features and design (interface simplicity, visual style), functionalities, preferences about the content, activities to be included in the mobile app and barriers to adoption and usage of the app. Adolescents and their parents will also share their experiences with the treatments received in the past, including the pros and cons related to the treatments received, and their preferences regarding the use of apps (and websites).

Additionally, we will conduct FGs with teachers to understand the needs within the school context (i.e., they will be asked about their knowledge of chronic pain, their experiences with students suffering with chronic pain, the needs they identify in the school context and the strategies and resources they consider useful) and develop the web page [i.e., we will gather their opinions and preferences about the (co)creation of a website to support students with chronic pain].

Moreover, we will also conduct FGs with healthcare professionals to discuss the treatments they provide, barriers to treatment, their experiences with individuals with chronic pain, and their experience with and position around the use of digital treatment in healthcare practice.

Finally, we will conduct a FG with health authorities to determine the key characteristics that would enhance DigiDOL-Ad's appeal for integration into the mainstream healthcare system and to identify strategies for simplifying and streamlining this process. All FGs will be audio recorded and transcribed verbatim. In addition, we will also conduct interviews at the end of each FG to ensure that did not miss any significant bit of information. Following the recommendation of Braun and Clarke (27), we will conduct focus groups until reaching the point of saturation. This refers to the stage where no new themes or codes emerge from the data (i.e., information redundancy). At this stage of the research, it is not possible to determine this point entirely in advance.

